**Methods/Design:**

The ARIQUELI study is a single-site, parallel-group, randomized, outcome assessor-blinded trial. BD I patients according to the DSM-IV-TR, in depressive, manic/hypomanic or mixed episode, aged 18 to 40 years, are eligible. After diagnostic assessments, patients initiated treatment in phase I with quetiapine. Nonresponders or partial responders after 8 weeks are allocated into one of two groups, potentiated with either lithium (0.5 to 0.8 mEq/l) or aripiprazole (10 or 15 mg). Patients will be followed up for 8 weeks in phase I (acute treatment), 6 months in phase II (continuation treatment) and 12 months in phase III (maintenance treatment). Outcome assessors are blinded to the treatment. The primary outcome is the evaluation of changes in mean scores on the CGI-BP-M between baseline and the endpoint at the end of each study phase.

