### Interventions

After diagnostic assessments, the patients initiate treatment with quetiapine for 8 weeks as described above. For acute treatment, patients shall receive a starting dosage of 100 mg on day 1, to be increased by 100 mg/day to 300 mg on day 3. The 300 mg dose shall be subsequently adjusted until reaching the most effective dose according to clinical criteria. The patient dose shall be determined according to individual tolerability, and a maximum dose of 800 mg will be allowed for this study. Patients showing remission or >50% reduction in baseline scores on the Hamilton Depression Scale and the Young Mania Rating Scale shall proceed to the maintenance phase for a further 18 months. Patients showing score reductions <50% on the scales will be allocated to one of the arms of the augmentation phase. Group I will receive lithium at the standard dose: starting at 300 mg daily, the weekly dose will be adjusted according to blood serum level (between 0.5 and 0.8 mEq/l) according to efficacy and tolerability. Group II will receive aripiprazole: starting at 10 mg daily, the dose will be adjusted up to 15 mg daily according to efficacy and tolerability. The only concomitant medications permitted are lorazepam at doses of 0.5 to 4 mg/day and biperiden at 2 to 8 mg/day.

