### Study phases

Patients will be followed up for 8 weeks in phase I (acute treatment), 8 weeks in phase II (potentiation treatment) and shall continue in phase III (maintenance) until study endpoint at 2 years. Scale raters will be blind to the treatment. Only patients that respond will continue to phase 3, with response determined according to the initial symptoms score in phase I. Patients in phase III using quetiapine alone that present a new episode of any polarity, as detected on two consecutive visits, will start phase II (potentiation treatment). Patients that show no response after phase II will be dropped from the study.

The definition of clinical course is defined as follows: no response, reduction ≤25% in severity of symptoms; partial response, improvement of 26 to 49% in symptoms; response, reduction ≥50% in severity of symptoms; remission, minimal or no symptoms for at least 1 week, Hamilton Depression Scale ≤7 and Young Mania Rating Scale ≤9; sustained remission, ≥8 weeks of remission; relapse/recurrence, return of the signs and symptoms for the syndrome as per criteria; and worsening, return of symptoms at subsyndromal level [28-30].

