### Secondary outcomes

Secondary outcome will include the proportion of patients that achieve remission and response to each treatment at the end of each phase of the study, according to improvement on the rating scales (Hamilton Depression Scale; Montgomery–Åsberg Depression Rating Scale; Young Mania Rating Scale) and in CGI-BP-M [31]. The CGI-BP-M is a clinician rating scale modified for BD for assessing treatment response and consists of three subscales evaluating severity of mania, depression and global disease symptoms.

Other outcome parameters include safety and tolerability, quality of life and social adjustment, and cognitive impairment. These parameters will be evaluated by comparing the endpoint measures for each phase with baseline values. Safety and tolerability were determined according to the clinical evaluation of adverse effects and score on the UKU side-effect rating scale [32]. The UKU comprises a 48-item clinician rated scale evaluating side effects in psychic, neurologic, autonomic and other domains. Quality of life and social adjustment were measured with the WHOQoL-BREF [33] and the Social Adjustment Scale [34]. These instruments were previously translated and validated into Portuguese [35,36]. The WHO-QOL-BREF is a 26-item self-report scale comprising four domains: physical, psychological, social, and environmental. The Social Adjustment Scale is a 54-question self-report instrument that measures instrumental and expressive role performance over the previous 2 weeks. Cognitive impairment was measured neuropsychological tests (Wisconsin Card Sorting Test, Stroop Color Word Test [37], Wechsler Abbreviated Scale of Intelligence [38], Trail Making Test [37] and others), for which versions are available in Portuguese. All investigators received appropriate training, and inter-rater reliability is periodically assessed.

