### Planned analyses

The primary analysis will entail evaluation of mean scores on the CGI-BP-M between baseline and endpoint in both groups. In addition, differences shall be evaluated by comparing the two treatment groups according to the total number of patients in full remission at the study endpoint and the reason for and timing of drop out. Continuous data will be represented as mean and standard deviation whereas categorical variables will be described by a table of frequencies. The results of all statistical comparisons of the treatment groups will be expressed as two-sided *P* values rounded to three decimal places. The criterion for statistical significance in all comparisons will be *P* ≤0.05.

Continuous variables will be compared using repeated-measures of analysis of variance, with the treatment group and study phase as factors. Rates of response, remission and dropouts will be compared between the two groups using Pearson's chi-square test for categorical data. Dichotomous measures will also be compared using odds ratios and 95% confidence limits.

The correlation of clinical issues, quality of life, social adjustment and cognitive impairment will be evaluated by Pearson's correlation.

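### Response is compared with an unstratified chi-square although the phase I reduction at allocation counts toward the response endpoint, so a chance imbalance at 25 per arm would go uncorrected

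*Protocol article*

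**What the plan says.** The relevant text is spread over several sections of the protocol article.

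- **Test.** Planned analyses: "Rates of response, remission and dropouts will be compared between the two groups using Pearson's chi-square test for categorical data". The same section adds: "Dichotomous measures will also be compared using odds ratios and 95% confidence limits". Neither sentence names a stratum or covariate.
- **Who is allocated.** Interventions: "Patients showing score reductions <50% on the scales will be allocated to one of the arms of the augmentation phase". The Abstract describes the same pool: "Nonresponders or partial responders after 8 weeks are allocated into one of two groups".
- **How the pool divides.** Study phases: "no response, reduction ≤25% in severity of symptoms; partial response, improvement of 26 to 49% in symptoms; response, reduction ≥50% in severity of symptoms".
- **Reference score.** Study phases: "Only patients that respond will continue to phase 3, with response determined according to the initial symptoms score in phase I". The improvement on quetiapine alone therefore counts toward the 50% needed after augmentation.
- **Status.** The Secondary outcomes section places response and remission there: "Secondary outcome will include the proportion of patients that achieve remission and response to each treatment at the end of each phase of the study". The primary outcome is change on the CGI-BP-M, and the Sample size section calls the study exploratory.

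Two further facts from Study phases limit the point. Remission is defined by absolute cut-offs (Hamilton 7 or less and Young Mania 9 or less), not by percentage reduction. Patients on quetiapine alone who have a new episode in phase III also start phase II.

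**The concern.** The endpoint definition links response after augmentation to what happened before augmentation. A patient allocated at a 45% reduction needs 5 more percentage points of the initial score to count as a responder; one allocated at 5% needs 45. That head start is known before the add-on is assigned, and the trial must record it to decide who is allocated.

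With about 25 patients per arm, chance can easily put more of the nearly-there patients in one arm. The crude response difference would then partly reflect who entered each arm, and no stated analysis would separate this from a difference between the add-ons. Planned analyses applies P ≤0.05 to every comparison, so such a difference could be reported as a finding.

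**Working it through.** **The plan's own figure.** The Sample size section gives 25 per group for 80% power at 5%, two-sided, for 0.8 SD. By the normal approximation, n = 2(1.960 + 0.842)² / 0.8² = 24.5, so 25 (power 80.7%; noncentral t gives 79.1%). The figure reproduces. It concerns the CGI-BP-M, not response, but it fixes the 25 per arm used below.

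**Size of the head start.** If a patient has already reduced by a fraction r, the further fall needed in the remaining score to reach 50% is 1 − 0.5/(1 − r).

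| Reduction at allocation | Further fall needed in remaining score |
|---|---|
| 0% | 50% |
| 10% | 44% |
| 25% | 33% |
| 26% | 32% |
| 40% | 17% |
| 49% | 2% |

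The gradient is steep from end to end but smooth, with almost no step at the 25/26% boundary.

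**Chance of an imbalance.** Let the number of partial responders in each arm be Binomial(25, f), with f assumed because the article gives no shares. By exact enumeration, the probability that the arms differ by 5 or more is 16.4% for f = 0.3, 19.3% for f = 0.4 and 20.3% for f = 0.5.

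**Effect of an imbalance.** A difference of 5 patients is 5/25 = 0.20 of an arm. With no treatment effect, the expected shift in the response difference is 0.20 × (partial-responder rate − non-responder rate):

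- 30% v 50%: 0.20 × 20 = 4 points
- 20% v 60%: 0.20 × 40 = 8 points
- 15% v 75%: 0.20 × 60 = 12 points

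In null trials with an imbalance of 5 or more (f = 0.5), Pearson's chi-square rejects in 7%, 11% and 17% for these three pairs by exact enumeration. In simulation (200,000 trials per scenario) the Cochran-Mantel-Haenszel (CMH) test stays at about 5%.

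**Average over all randomisations.** For these pairs, with f from 0.3 to 0.7, Pearson's overall false-positive rate is 5.4% to 6.4% and CMH's 4.8% to 5.0%. When the two strata have equal rates, Pearson is still at 5.9% to 6.0%. Exact sizes at 25 v 25 without strata are 4.9%, 6.0% and 6.5% at true rates of 10%, 40% and 50%. The small excess is thus a small-sample feature of the uncorrected test, not a result of pooling strata.

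**Power.** Assumed common odds ratio 5.5, f = 0.5:

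| Control rates (non-responder / partial) | Pearson | CMH |
|---|---|---|
| 40% / 40% | 84% | 81% |
| 30% / 50% | 82% | 80% |
| 20% / 60% | 72% | 74% |
| 15% / 75% | 53% | 64% |

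Pearson's advantage in the first two rows is obtained at a false-positive rate about 1 point higher (5.9% to 6.0% against 4.9% to 5.0%).

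**The case against.** The strongest reply is that nothing here is wrong. Allocation is random, and an unstratified two-group comparison is valid under randomisation; pooling prognostic strata costs precision and does not bias the comparison. A reader might infer from the 7% to 17% rejection rates that the planned test is badly oversized. It is not: those rates are conditional on an imbalance having occurred. This part of the objection stands in full.

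A reader might also infer that the phase I result largely decides who can reach 50%. The article has no response rate by earlier response and no expected share of either group. Any allocated patient can still reach 50%, and the head start is graded. Only "likely to predict" can be supported.

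Three more objections stand in part. Remission rests on absolute cut-offs, so the head-start arithmetic does not carry over to it. Two strata would leave no place for patients who enter phase II after a new episode on quetiapine alone. And stratification does not always gain power: it loses 2 to 3 points if the phase I result predicts weakly.

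Finally, covariate adjustment is often left to a fuller document. That would excuse silence, but Planned analyses is not silent: it names the crude test for response, and the proposal is to change that stated choice.

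**Conclusion.** The point holds as an improvement to a secondary outcome, of minor to moderate weight. The stated test for response ignores a factor that the endpoint definition itself makes likely to be prognostic. At 25 per arm, an imbalance of 5 or more partial responders is expected in about 16% to 20% of trials; a 5-patient imbalance moves the expected response difference by about 4 to 12 points with no planned correction. The first range assumes that 30% to 50% of allocated patients are partial responders. The second assumes stratum response rates 20 to 60 points apart.

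The main argument is protection against chance imbalance. The power effect runs from a loss of 2 to 3 points (stratum gaps of 0 to 20 points) through a gain of about 2 (40-point gap) to about 11 (60-point gap). The documents do not support calling the crude test biased or invalid, attributing its slight excess size to the mixing of strata, or applying the same argument to remission.

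**What to change.** In Planned analyses, for response at the end of phase II and later, replace Pearson's chi-square by one of the following, chosen in advance:

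- a Cochran-Mantel-Haenszel test stratified by phase I result at allocation, with three categories: no response, partial response, and entry to phase II after a new episode on quetiapine alone; or
- a logistic model adjusted for percentage reduction at allocation, which suits the graded head start better.

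Report the stratified odds ratio and risk difference with 95% limits. For remission, report the stratified analysis as supportive only. Assign the category by the same scale rule that decided allocation, so that it is unambiguous when the scales disagree.

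The cost is a sentence or two, using data the trial already needs in order to allocate patients. No change to the allocation list is needed. The downsides are that the odds ratio becomes conditional on stratum, and that power may fall by 2 to 3 points if the phase I result predicts response only weakly. The article reports the trial as still in progress, so the change should be fixed before outcomes are compared by arm.

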## Discussion

Trials comparing specific treatment efficacy in BD (head to head) can show relevant information in clinical practice.

Typical limitations in clinical trials include: specific clinical forms of BD (mania/mixed or depression) for each treatment tested; scant information available on how treatment in the acute phase should progress to maintenance or which factors in acute treatment predict recurrence during maintenance treatment; and heterogeneity of patients, considering the course of illness (chronic versus nonchronic) in clinical trials can mask important treatment implications for specific populations (younger versus older, for example).

Owing to the substantial increase in treatment options, specific guidelines and algorithms are used in an effort to enhance the cost-effectiveness of care by minimizing the number of treatment options employed [28]. Despite limitations inherent to the use of these algorithms, they represent the available data concerning the levels of evidence for each treatment option.

Further evidence-based knowledge concerning augmentation strategies and maintenance therapy using combination treatments is needed in clinical practice.

## Current trial status

The ARIQUELI study is currently in progress, with patients in phases I, II and III, and is to be extended for a further 2 years.

## Abbreviations

BD: Bipolar disorder; CGI-BP-M: Clinical Global Impression for Bipolar Disorders; DSM-IV-TR: Diagnostic and Statistical Manual of Mental Disorders, 4th Edition, Text Revision.
